### Sample size

2.3

The present study is powered based on the primary outcome; percentage total brain volume change after 24 weeks of PRE in pwMS quantified by structural image evaluation, using normalization, of atrophy (SIENA) [41] and the assumption that PPT is ∼15% more effective than traditional of PRE [49,54]. A two-sample two-sided power calculation showed that a total of 30 subjects are needed in each group to adequately power the study (α = 0.05; power = 0.8; control mean = 0.3204 (SD 0.5253); exercise mean = −0.0148 (SD 0.2698); dropout rate = 16%).

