#### Primary outcome

2.6.1

The primary outcome of the study is MRI-derived whole brain atrophy rate measured using SIENA [59]. All MRI scans will be performed on the same 3-T MRI scanner (MAGNETOM Skyra, Siemens Medical Systems, Erlangen, Germany) at baseline, 24 weeks (post-intervention), and 48 weeks (follow-up). MRI analyses will be performed by a blinded assessor. Annualized whole brain atrophy rate is quantified using structural T1-weighted 3D Magnetization Prepared 2 Rapid Acquisition Gradient Echo images [60] acquired with a Field-of-view (FOV) of 256 × 256 mm^2^, matrix of 256 × 256, spatial resolution of 1 × 1 × 1 mm^3^. Repetition time (TR) is 5000 ms, Echo time (TE) is 2.98 ms and Inversion time (TI) is 707 ms/2500 ms. The image processing will follow the steps outlined by Riemenschneider et al. [61].

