### Statistics

2.8

Characterization of the study sample across groups will be carried out using multiple baseline demographic and anthropometric variables (reported as number of observations, mean ± SD or median ± IQR, and proportions were appropriate). Data is checked for normality via visual inspection of histograms and quantile-quantile plots. In case of non-normality, appropriate data transformations will be performed. To investigate the effect of the 24 weeks PPT intervention and the 24 weeks follow-up period on the primary outcome (i.e., whole brain atrophy rate), a linear mixed model with repeated measures is used with group and time as fixed effects and participant id as random effects. The secondary outcomes will be analyzed analogous to the primary outcome. The analyses are performed following the intention-to-treat principle (i.e., all participant data are included, but without use of “last observation carried forward”) as the mixed model allows for missing value. In addition, a per-protocol analysis is performed based on adherence levels (only including participants that attend ≥80% of the planned PPT training sessions). An alpha level of 0.05 is used for all comparisons.

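### The stated mixed model conditions on no baseline value, and for the SIENA outcome it covers only participants with a post-baseline scan

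*Protocol article*

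**What the plan says.** All references are to the protocol article.

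- **Statistics (2.8).** The primary outcome is analysed with a linear mixed model for repeated measures, with group and time as fixed effects and participant as random effect. Secondary outcomes are analysed in the same way. The intention-to-treat statement is that "all participant data are included, but without use of “last observation carried forward”) as the mixed model allows for missing value". No other handling of missing values is given.
- **Use of baseline data (2.8).** "Characterization of the study sample across groups will be carried out using multiple baseline demographic and anthropometric variables". No baseline variable is named as a term in the model.
- **When baseline is measured.** Under Random allocation procedure (2.4), randomisation follows baseline testing. Outcomes (2.6) and Table 3 place all outcomes at weeks 0, 24 and 48, with EDSS at baseline only.
- **Primary outcome (2.6.1).** "The primary outcome of the study is MRI-derived whole brain atrophy rate measured using SIENA", from scans at baseline, week 24 and week 48.
- **Sample size (2.3).** "A two-sample two-sided power calculation showed that a total of 30 subjects are needed in each group", with "α = 0.05; power = 0.8" and a 16% dropout allowance. The Discussion names dropout above 16% as a risk to power and cites 0 to 47% from younger patients.

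**The concern.** Two features of the stated model deserve attention.

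First, age, EDSS, the baseline MRI and nearly all secondary outcomes are known before randomisation, yet the model conditions on none of them. For a secondary outcome with a week-0 value, baseline enters as one more response, with a separate mean for each arm. The treatment contrast at week 24 is then in effect a difference in change scores, which is less precise than a comparison conditional on baseline. With about 25 evaluable participants per arm, precision matters.

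Second, the stated reason why missing values are harmless does not carry over fully to the primary outcome. SIENA measures change between two scans, so it has no value at week 0. A participant with only the baseline scan has no response for the mixed model to use. At stake is an accurate description of who is in the primary analysis, and possible bias if those without a later scan differ in prognosis.

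**Working it through.** **1. The plan's own sample size.** Inputs from Sample size (2.3): control mean 0.3204 (SD 0.5253), exercise mean −0.0148 (SD 0.2698), two-sided α 0.05, power 0.8, dropout 16%.

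- Difference: 0.3204 − (−0.0148) = 0.3352.
- Root-mean-square SD: √[(0.5253² + 0.2698²)/2] = 0.4176. Standardised difference: 0.80.
- The normal approximation gives 25 evaluable per group, and 25/0.84 = 29.8, so 30. The stated figure is reproduced. A t-based calculation gives 26, or 31 after inflation.
- With 25 per group, SE = 0.4176 × √(2/25) = 0.1181 and 0.3352/0.1181 = 2.84, so normal-approximation power is 81.0% (78.9% by a Welch t calculation).

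**2. Secondary outcomes with a week-0 value.** Assume equal variance σ² at both times, correlation ρ between baseline and week 24, complete data, and a group-by-time contrast read into the model.

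- Variance per participant, change score: 2σ²(1 − ρ).
- Variance per participant, conditional on baseline: σ²(1 − ρ²).
- Ratio: (1 − ρ²)/[2(1 − ρ)] = (1 + ρ)/2. Reduction: (1 − ρ)/2.

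| Assumed ρ | Ratio | Reduction |
|---|---|---|
| 0.5 | 0.75 | 25% |
| 0.7 | 0.85 | 15% |
| 0.8 | 0.90 | 10% |

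Estimating one slope with 50 analysed participants multiplies the conditional variance by about 1 + 1/(50 − 1 − 3) = 1.022, which trims each reduction by about 2 percentage points.

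**3. Primary outcome with baseline covariates.** Let ρ be the (multiple) correlation of the covariates with SIENA change. The documents do not give it, so a range is shown. Residual variance is multiplied by 1 − ρ², with 25 evaluable per group.

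| Assumed ρ | 1 − ρ² | Power, normal approximation | Power, Welch |
|---|---|---|---|
| 0 (as planned) | 1.00 | 81.0% | 78.9% |
| 0.1 | 0.99 | 81.4% | 79.3% |
| 0.3 | 0.91 | 84.5% | 82.5% |
| 0.5 | 0.75 | 90.6% | 89.0% |

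These figures leave out the cost of estimating the slopes. For three covariates that cost multiplies the variance by about 1 + 3/(50 − 3 − 3) = 47/44 = 1.068. The break-even is therefore a joint R² of 3/47 = 0.064, a correlation of about 0.25. Below that, three covariates bring no net gain.

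**4. Who enters the primary model.** With SIENA change as the response, a participant contributes through a week-24 value, a week-48 value or both. With neither, there is no row. A simulated change-score mixed model with 60 participants, 10 of them without any post-baseline value, shows this: fitted with or without those 10, the group estimate (0.2683) and standard error (0.0916) are identical. If all of the planned dropout were of this kind, 0.16 × 60 = 9.6, so about 10 of 60 would be outside the model.

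**The case against.** The strongest reply is that this is a condensed article and that covariates, analysis sets and sensitivity analyses usually belong in a statistical analysis plan, which is not shown. That holds for imputation and other sensitivity analyses, whose absence here is no fault. It holds less well for the model, because the article states its terms and extends them to every secondary outcome.

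Several stronger readings are tempting, and the documents do not support them:

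- **That the intention-to-treat statement is false.** It speaks of including all participant data, not of every randomised participant having an outcome. For SIENA it is loose, not contradictory.
- **That the primary analysis is complete-case.** A participant scanned at only one of weeks 24 and 48 still contributes.
- **That 10 of 60 will be lost.** This is an upper figure at the planned dropout. Someone who stops training may still be scanned.
- **That dropout at 16% erodes planned power.** The step from 25 to 30 per group already covers it, and the Discussion discloses the risk above 16%.
- **That chance imbalance invalidates the unadjusted comparison.** Under randomisation it remains valid; adjustment is a matter of precision.
- **That dropout is related to disability or arm.** This is plausible when only one arm attends supervised training, but nothing in the article establishes it.

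It is also fair that some secondary MRI outcomes are defined as percentage changes, so the repeated-baseline argument does not clearly apply to them. For secondary outcomes with a week-0 response, baseline-only participants do enter the model.

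**Conclusion.** The point stands as an improvement worth making and a description worth correcting, not as an error that undermines the trial. For secondary outcomes recorded at week 0, conditioning on baseline gives a variance reduction of 25% to 10% over assumed correlations of 0.5 to 0.8, relative to a change-score contrast with equal variances and complete data. For the primary outcome the gain is uncertain: 0.4, 3.5 or 9.6 percentage points of power at assumed correlations of 0.1, 0.3 or 0.5 before the cost of estimation, and no net gain from three covariates below a correlation of about 0.25.

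The mixed model does not by itself secure a primary analysis of all randomised participants; it covers those with at least one post-baseline scan. Baseline covariates do not bring the others back. What remains is possible bias, which the documents give no means of sizing.

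**What to change.** - **Secondary outcomes with a week-0 value:** constrain the two arms to a common baseline mean in the mixed model, or use the baseline value as a covariate.
- **Primary outcome:** add a few prespecified baseline covariates to the SIENA model, for example age, EDSS and normalised brain volume. Keep the list short and choose variables expected to predict atrophy, given the break-even above.
- **Wording:** describe the primary analysis as covering participants with at least one post-baseline scan, instead of relying on the mixed model's tolerance of missing values.
- **Optional:** a sensitivity analysis that imputes missing SIENA values from baseline variables.

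The cost is a few sentences and about 3 of about 48 degrees of freedom (25 + 25 − 2) in the primary analysis. No new data are needed. If an existing analysis plan already contains these terms, only the description of the primary analysis needs aligning.

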For the primary aim, we test the hypothesis that older pwMS performing 24 weeks of power training will elicit a reduced annualized whole brain atrophy rate compared with the control group. For the secondary aim we test the hypothesis that performing 24 weeks of power training will improve brain micro and macro structures, neuromuscular, physical, cognitive function, bone health, and patient-reported outcomes.

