### Outcomes

2.6

All outcomes will be assessed at week 0, 24, and 48. An overview of outcomes can be seen in Table 3.

**Table 3 tbl3:** Overview of test.

	Pre intervention test	Post intervention test	Follow-up test
Brain MRI			
MP2RAGE	x	x	x
T2 Space, dark fluid	x	x	x
DKI	x	x	x
Leg MRI			
Leg 2D Dixon	x	x	x
Muscle strength			
Bilateral leg press	x	x	x
Hand grip	x	x	x
Knee extension	x	x	x
Knee flexion	x	x	x
Plantar ankle flexion	x	x	x
Dorsal ankle flexion	x	x	x
Neural function			
ITT	x	x	x
EMG	x	x	x
Cognition			
SRT	x	x	x
SDMT	x	x	x
Clinical disability			
EDSS	x		
Physical function			
T25FWT	x	x	x
SSST	x	x	x
6MWT	x	x	x
9SSA	x	x	x
NHPT	x	x	x
1STS	x	x	x
5STS	x	x	x
Standing balance	x	x	x
Blood sample			
Neurodegenerative factors	x	x	x
Neurotrophic factors	x	x	x
Immunological factors	x	x	x
Bone metabolism	x	x	x
Body composition			
DXA	x	x	x
Physical activity			
Accelerometry	x	x	x
Questionnaires			
MSIS	x	x	x
MSWS	x	x	x
HADS	x	x	x
MFIS	x	x	x
EQ5D	x	x	x
FES-I	x	x	x
PSQI	x	x	x
ADL	x	x	x
BPI	x	x	x

Abbreviations: MP2RAGE: Magnetization Prepared 2 Rapid Acquisition Gradient Echo, DKI: Diffusion kurtosis imaging, T25FWT: Timed 25-foot walk test, SSST: Six spot step test, 6MWT: Six-minute walk test, 9SSA: Nine step stair accent, NHPT: Nine-hole peg test, 1STS: one time sit-to-stand test, 5STS: five time sit-to-stand test, SRT: Selective reminding test, SDMT: Symbol digit modality test, EDSS: Expanded disability status scale, DXA: Dual-energy X-ray absorptiometry MSIS: Multiple sclerosis impact scale, MSWS: Multiple sclerosis walking scale, MFIS: Modified fatigue impact scale, HADS: Hospital anxiety and depression scale, EQ-5D: Euro quality of life 5-dimension, FES-I: Falls efficacy scale-international, PSQI: Pittsburgh sleep quality index, ADL: Activities of daily living, BPI: Brief pain inventory.

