#### Secondary outcomes

2.6.2

Analysis of macrostructural changes of brain tissue based on T1 weighted images consists of percentage change in brain parenchymal fraction, white matter volume, grey matter volume, and cortical thickness using FACE [62]. Whole brain white matter lesion load and lesion count are derived from fluid attenuated inversion recovery (FLAIR) images using LST [63]. The FLAIR sequence is a 3D SPACE sequence with FOV = 250 × 364 mm^2^, matrix = 220 × 320, and spatial resolution = 1.1 × 1.1 × 1.2 mm^3^. TR/TE/TI = 5000/386/1800 ms.

To study brain microstructure a diffusion kurtosis imaging (DKI) sequence is applied. From this, a range of parameters describing the tissue microstructure can be derived. These include fractional anisotropy, mean diffusivity, axial diffusivity, radial diffusivity, axonal signal fraction, intra-axonal diffusivity, extra-axonal axial diffusivity, and extra-axonal radial diffusivity. Finally, the DKI sequence is utilized to measure white matter fibre orientations by calculating tractography maps. These are important for understanding the association between functional symptoms and structural connections affected by white matter lesions. DKI is based on single-shot diffusion weighted EPI sequence with b-values of 250, 1000 and 2000 s/mm^2^ and 84 diffusion directions in total. FOV is 216 × 216 mm^2^, matrix is 128 × 128, and spatial resolution is 1.7 × 1.7 mm^2^ with a slice thickness of 3 mm. TR/TE is 9300/97 ms.

The PPT intervention is expected to affect brain regions involved in motor function [[64], [65], [66], [67], [68], [69], [70]]. Thus, a separate analysis for these regions is conducted. The following nuclei are segmented and processed to study changes in macro- and microstructure: thalamus, hippocampus, putamen, caudate, globus pallidus, corticospinal tract, cingulate gyrus, corpus callosum, cervical spinal volume, and motor cortex.

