## Discussion and perspectives

3

We have presented the protocol for a trial that evaluates the neuroprotective effect of PPT in older pwMS, specifically evaluating whole brain atrophy rate (primary outcome). To our knowledge, neither PPT nor exercise in general have previously been investigated for its effect on brain morphology in older pwMS, despite this population constituting approximately one-third of all pwMS [[7], [8], [9]]. The presented study secondarily evaluates the effects of PPT on macro and micro brain structures, neuromuscular function, physical function, cognitive function, bone health and patient-reported outcomes, which we believe will expand the current knowledge of PPT in pwMS [36].

A limitation of the presented study is that the primary outcome (i.e., whole brain atrophy rate) has recently been shown to remain almost unaffected following 24–48 weeks of aerobic exercise in two large RCT's. In contrast, PRE, although sparsely investigated, have shown positive effects on CNS morphology in one pilot RCT by Kjølhede et al. [41]. Speculatively, the difference in exercise modality and hence physiological response could account for these discrepancies in the effect of exercise on CNS morphology.

Another potential limitation regarding the primary outcome is that the power calculation is based on an expected dropout rate of 16%. The lack of studies investigating PPT in older pwMS limits our knowledge of dropout in this subpopulation of pwMS. In young and middle-aged pwMS a dropout of 0–47 % has been reported across exercise interventions and adherence to progressive resistance exercise interventions of 91 % is found in a systematic review and meta-analysis [126]. Therefore, the presented study could be at risk of having reduced statistical power to detect true changes if the dropout exceeds the 16 % applied in the power calculation. Further, if changes are detected there is limited knowledge on how large a change in global brain atrophy rate is needed to make a clinically meaningful change. However, it is assumed that any reduction in global brain atrophy rate is valuable.

The presented study is expected to be finalized mid-2024, and the findings have the potential to guide clinically meaningful interventions for older pwMS.

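### Secondary outcomes are worded as hypothesis tests in six domains, each at 0.05, with no ordering and almost no supportive or exploratory label

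*Protocol article*

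**What the plan says.** The last paragraph of the Introduction states the secondary aim as a test with a direction: "For the secondary aim we test the hypothesis that performing 24 weeks of power training will improve brain micro and macro structures". The same sentence goes on to neuromuscular, physical and cognitive function, bone health and patient-reported outcomes, which makes six domains.

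Statistics (2.8) then fixes how these are handled: "The secondary outcomes will be analyzed analogous to the primary outcome", and "An alpha level of 0.05 is used for all comparisons".

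Outcomes (2.6) sets the time points: "All outcomes will be assessed at week 0, 24, and 48". Secondary outcomes (2.6.2) adds a block for motor-related brain areas, ten of which are listed: "Thus, a separate analysis for these regions is conducted".

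The article names no key secondary outcome and no testing order. The one place with exploratory language is Blood markers (2.6.2.4), which speaks of exploring the effect of training on the biomarkers.

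**The concern.** Unadjusted secondary tests are ordinary practice when they are labelled supportive. The difficulty here is the combination of two printed statements: a secondary hypothesis worded as something the trial tests, and one nominal level for every comparison. Nothing separates a result the trial set out to establish from one of several dozen looks at the data.

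The trial has 60 participants and is powered on the primary outcome only. Discussion and perspectives (3) acknowledges that whole brain atrophy rate was almost unaffected in two large trials of aerobic exercise. If the primary result here is also null, attention will move to the secondary outcomes. As worded, the article would let an isolated p<0.05 be presented as a tested hypothesis that was confirmed.

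**Working it through.** **The plan's own figures.** The article gives no family-wise error rate for the secondary outcomes. Its only error-rate calculation is the sample size for the primary outcome (2.3), and that reproduces. The difference is 0.3204 + 0.0148 = 0.3352, and the pooled SD is √((0.5253² + 0.2698²)/2) = 0.4176. The normal approximation gives n = 2(1.960 + 0.842)² × 0.4176²/0.3352² ≈ 24.4, so 25 evaluable per group. Then 25/0.84 = 29.8, or 30 per group as stated.

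**Count of tests (from Table 3).** Rows measured at weeks 0, 24 and 48:

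| Block | Rows |
|---|---|
| Brain MRI, without MP2RAGE (the primary's sequence) | 2 |
| Leg MRI | 1 |
| Muscle strength | 6 |
| Neural function | 2 |
| Cognition | 2 |
| Physical function | 8 |
| Blood sample | 4 |
| Body composition | 1 |
| Physical activity | 1 |
| Questionnaires | 9 |
| **Total** | **36** |

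EDSS is excluded because it is baseline only. Many rows split into several named endpoints: 8 diffusion parameters, 7 muscle areas, 12 isokinetic-dynamometer conditions (4 muscle groups × 3 contraction types) and 15 blood markers. A fuller count gives about 96 per time point. Week 48 and the per-protocol analysis are further comparisons, not counted here.

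**Model (assumption).** All k nulls are true, the test statistics are standard normal with common correlation r, and each is tested two-sided at 0.05 (c = 1.96). With Z standard normal:

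- either direction: 1 − E[{Φ((c − √r Z)/√(1−r)) − Φ((−c − √r Z)/√(1−r))}^k]
- false improvement only: 1 − E[Φ((c − √r Z)/√(1−r))^k]

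At r = 0 these reduce to 1 − 0.95^k and 1 − 0.975^k.

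**Results (at least one false positive).**

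| Tests | Direction | r = 0 | r = 0.5 | r = 0.8 |
|---|---|---|---|---|
| 6 (one per domain) | either | 0.26 | 0.21 | 0.14 |
| 6 | improvement only | 0.14 | 0.10 | 0.07 |
| 36 (Table 3 rows) | either | 0.84 | 0.55 | 0.27 |
| 36 | improvement only | 0.60 | 0.28 | 0.14 |

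The expected number of false positives under the global null does not depend on correlation: 36 × 0.05 = 1.8 in either direction and 36 × 0.025 = 0.9 for improvements.

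**Sensitivity.**

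- *Blood markers set aside.* Without the four blood rows, k = 32. At r = 0 the rates are 1 − 0.95^32 = 0.81 and 1 − 0.975^32 = 0.56.
- *Half the effects real.* With 18 true nulls, the rates at r = 0 are 1 − 0.95^18 = 0.60 and 1 − 0.975^18 = 0.37. At r = 0.5 they are 0.40 and 0.20.
- *Named endpoints.* For 96 tests, block-correlation simulations (within-block 0.5 to 0.7, between-block 0.1 to 0.3) gave 0.83 to 0.95 in either direction and 0.48 to 0.68 for improvements.

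**The case against.** Several counter-arguments have force.

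- **The size depends on the event and the correlation.** A reader might infer that at least one false improvement is more likely than not. The documents do not support that as a general statement. For 36 tests the improvement-only rate is 0.28 at correlation 0.5, and it exceeds one half only up to a correlation of about 0.1. Even in either direction it falls to 0.27 at correlation 0.8.
- **A global null is implausible for some outcomes.** The Introduction cites evidence that resistance exercise improves strength and physical and neuromuscular function. Outcomes with real effects cannot give false positives, so the rates above are upper figures for the assumed count and correlation.
- **No decision rule is printed.** A reader might also infer that any single p<0.05 counts as support for the secondary hypothesis. The article does not say so. It joins the domains with *and*, and elsewhere it speaks of evaluating these effects.
- **The primary outcome is safe.** There is one prespecified, powered primary outcome, and no number of secondary tests changes its error rate.
- **Table 3 lists tests and scans, not endpoints.** The count is therefore approximate. Accelerometry and some of the blood rows also lie outside the six domains.
- **An article may leave multiplicity to an analysis plan.** That would answer a complaint about silence. This article is not silent: it prints both a level for all comparisons and a hypothesis-testing aim, and both can be corrected where they stand.

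The first five points limit the size of the concern. They do not remove the mismatch between confirmatory wording and unordered testing at 0.05.

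**Conclusion.** The concern holds as a fault of framing. The article words the secondary aim as a directional test in six domains and applies 0.05 to every comparison. It gives no ordering, and its only exploratory language concerns the blood markers.

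Under the global null, the chance of at least one false positive among the 36 rows is well above 0.05: 0.84 to 0.27 in either direction over correlations 0 to 0.8. For improvements alone it is 0.60 to 0.14, against 0.025 for a single test. Splitting rows into named endpoints raises these figures, and real effects lower them. The article gives neither a total count of outcomes nor their correlations, so these are ranges under stated assumptions rather than estimates for this trial.

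The consequence is confined to what may be claimed from the secondary outcomes.

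**What to change.** In Statistics (2.8), replace the sentence on alpha with text to this effect: two-sided alpha 0.05 applies to the primary outcome; all secondary outcomes and all week-48 comparisons are exploratory or supportive, reported as estimates with 95% confidence intervals without adjustment for multiplicity, and not used for confirmatory efficacy claims. In the last paragraph of the Introduction, reword the secondary hypothesis so that the trial explores whether training improves these outcomes.

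If confirmatory secondary claims are wanted, a short list of named outcomes tested by Holm after a significant primary result is one option. It is not required, and making strength or function results depend on brain atrophy is a debatable trade-off.

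The cost is wording only, with no extra participants, data or procedures. The small downside is that an isolated secondary p<0.05 can no longer be presented as a confirmed effect.
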